## **5.5 Premature Termination of the Trial**

The clinical trial may be terminated prematurely or suspended at the request of Health Authorities or if new safety or efficacy information leads to an unfavourable risk benefit judgment for any IMP. The Sponsor may discontinue the trial if it becomes unjustifiable for medical or ethical reasons, for poor enrolment, or because of discontinuation of clinical development of an IMP or withdrawal of an IMP or comparator from the market for safety reasons.

Health Authorities and Independent Ethics Committees (IECs)/Institutional Review Boards (IRBs) will be informed about the discontinuation of the trial in accordance with applicable regulations.

## **5.6 Definition of End of Trial**

End-of-study evaluations will be performed at end of tasting period. End-of-study evaluations must also be performed when a subject prematurely terminates the study.

A clinical trial protocol may not be considered closed as long as:

- Any subject is still receiving any IMP,
- Visits specified by the protocol are still taking place,
- Procedures or interventions according to the protocol are still being undertaken in any subject,
- The post-treatment follow up period, defined in the clinical trial protocol as being part of the trial, has not yet been completed for any subject.

## 6 Investigational Medicinal Product(s) and Other Drugs Used in the Trial

### 6.1 Description of Investigational Medicinal Product(s)

#### MSC 2499550A (referred to as L-PZQ)

Chemical Name: (11bR)-2-(Cyclohexylcarbonyl)-1,2,3,6,7,11b-hexahydro-4H-pyrazino[2,1-a]isoquinolin-4-one

Recommended International Nonproprietary name (rINN): R-(-)-Praziquantel

Company or Laboratory Code: MSC2499550A

Molecular Formula:  $C_{19}H_{24}N_2O_2$

Relative Molecular Mass: 312.4 g/mol

White or almost white, crystalline powder.

MSC2499550A is presented as 150 mg strength ODT.

The tablet consists of MSC2499550A combined with the following pharmaceutical grade excipients: Maize starch, mannitol, sucralose, magnesium stearate and colloidal silicon dioxide.

#### MSC 1028703A (referred to as rac-PZQ)

Chemical Name: (11bRS)-2-(Cyclohexylcarbonyl)-1,2,3,6,7,11b-hexahydro-4H-pyrazino[2,1-a]isoquinolin-4-one

Recommended International Nonproprietary name (rINN): (RS)-Praziquantel

Company or Laboratory Code: MSC1028703A

Molecular Formula:  $C_{19}H_{24}N_2O_2$

Relative Molecular Mass: 312.4 g/mol

White or almost white, crystalline powder.

MSC1028703A is presented as 150 mg strength ODT.

## Praziquantel (Cesol® 600 mg)

Recommended International Nonproprietary name (rINN): (RS)-Praziquantel

Relative Molecular Mass: 312.4 g/mol

The tablet, which is available in Tanzania through the WHO donation program, consists of pharmaceutical grade excipients: sodium lauryl sulfate, magnesium stearate, corn starch, microcrystalline cellulose and povidone.

## 6.2 Dosage and Administration

The tasting will last 2 days for each subject. On each day, the test will start in the morning after breakfast. The composition of the breakfast will be documented as it will be offered to the study participants by the study team and therefore it will be the same for each subject.

For treatment arm 5, PZQ tablets (Cesol®) will be crushed and suspended in water and ¼ of the suspension (around 150 mg) will be administered directly in the buccal cavity using a syringe.

The child will be asked to hold the suspension for 10 sec in its mouth and will then spit out the liquid in a waste container. Rinsing with water to ensure all particles have been cleared off the mouth will be done after the spitting of the liquid. A mouth check will be performed after rinsing to ensure that no particles remain in the oral cavity. If any IMP particles are visible the child should be asked to rinse its mouth again with water and a recheck is performed.

For all treatments arms detailed preparation and administration instructions will be available in a separate document before the start of the study.

### 6.3 Assignment to Treatment Groups

Subjects will receive their subject identification number after the parents/guardians have signed their informed consent and the subject their assent. Subjects who meet all inclusion criteria and none of the exclusion criteria will be randomized after recheck of eligibility on Day 1.

The Investigator or delegate will allocate a randomization number to each subject in each stratification group, in sequential order before first tasting of IMP.

48 children (1:1 female/male ratio) will be included in the study.

The children will be randomized in blocks of gender and age (6 to <9 year old and  $\geq 9$  to <12 years old) in the order in which they are enrolled according to a randomization schedule prepared by Swiss TPH. Sequential randomly assigned numbers will be kept in sealed envelopes for each individual subject.

After signature of the informed consent and assent and the inclusion/exclusion criteria have been confirmed, the Investigator will open the next envelope corresponding to the correct gender and age group to assign the sequence in which the child will have to assess the tastes of the different treatments.

The randomization code consists of a single letter for the sequence in Day 1 and a letter for Day 2 is provided in table 2.

**1** stands for administered by putting on the tongue (always done on Day 1)

**2** stands for administered by dispersing/crushing in water (always done on Day 2)

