**Table 2 Randomization codes and sequences**

| Randomization code | DAY 1                             |                                    |
|--------------------|-----------------------------------|------------------------------------|
|                    |                                   |                                    |
| F1                 | Rac-PZQ ODT put on the tongue (B) | L-PZQ ODT put on the tongue (A)    |
| G1                 | L-PZQ ODT put on the tongue (A)   | Rac--PZQ ODT put on the tongue (B) |
|                    | DAY 2                             |                                    |

|    |                                             |                                             |                                             |
|----|---------------------------------------------|---------------------------------------------|---------------------------------------------|
| H2 | L-PZQ ODT dispersed in water (C)            | Rac-PZQ ODT dispersed in water (D)          | PZQ formulation 150 mg crushed in water (E) |
| J2 | L-PZQ ODT dispersed in water (C)            | PZQ formulation 150 mg crushed in water (E) | Rac-PZQ ODT dispersed in water (D)          |
| K2 | Rac-PZQ ODT dispersed in water (D)          | PZQ formulation 150 mg crushed in water (E) | L-PZQ ODT dispersed in water (C)            |
| L2 | Rac-PZQ ODT dispersed in water (D)          | L-PZQ ODT dispersed in water (C)            | PZQ formulation 150 mg crushed in water (E) |
| M2 | PZQ formulation 150 mg crushed in water (E) | L-PZQ ODT dispersed in water (C)            | Rac-PZQ ODT dispersed in water (D)          |
| N2 | PZQ formulation 150 mg crushed in water (E) | Rac-PZQ ODT dispersed in water (D)          | L-PZQ ODT dispersed in water (C)            |

The pharmacist will perform the randomization by taking the next envelope corresponding to the child's gender and age.

In order to avoid assignment errors the envelopes for boys and girls will be of different colour and the envelopes for the two age groups will also differ (e.g. blue envelopes for boy and age group 6-9 years has a different sticker than age group 9-11). In the randomization envelope there will be the code for the sequence of taste assessment for all 5 treatments (i.e. for both days).

If a volunteer does not show up on Day 2, swallows more than 1 medication or cannot assess all 5 taste assessments he/she will be replaced by a volunteer of the same sex and age group.

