#### **6.10 Method of Blinding**

All oral suspension formulations will be prepared by study personnel (pharmacist) in another location than the area where the taste tests will be conducted. Immediately prior to tasting, a small amount of the assigned formulation will be drawn into a plastic syringe identified by a number. All oral suspensions will be drawn into identical syringes which have been wrapped with tape obscuring the content to minimize bias and blind the subjects and the investigator from the identity of the formulation.

All breaks of the trial blind must be adequately documented.

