## 7 Trial Procedures and Assessments

### 7.1 Schedule of assessments

#### 7.1.1 Screening procedures

During two weeks of the initial screening period all eligible study subject who are 6-11 years old will be identified in a primary school setting among pupils who are in class two up to class five. An informed consent will be obtained from the parents of the pupils that seem eligible to participate in the taste study. The pupils will be further asked an assent to participate in the study. Those pupils will then be trained to taste different flavour of juice, keep a candy in the mouth for 20 sec. without swallowing it and the use of hedonic scale for interpreting their feelings. Before the actual randomization all pupils will be further examined for their health status.

In order to be able to include 48 volunteers in the study some additional volunteers (from all sexes and age groups) will be asked to come back on Day 1 in morning at about 2 hour prior to the first taste test.

#### 7.1.2 Study Day 1

On Day 1 a breakfast will be offered to all volunteers and after the physical examination, vital sign assessment and recheck of eligibility the randomization assignment will be done such that to balance the sequence of the palatability assessment in order that every formulation is tasted on an equal number of times between gender and the age groups.

According to gender and age, each subject will be randomized to receive a code to define the taste assessment sequence. These sequences will run from F1 and G1 for Day 1 tastes and H2-N2 all denoting permutations for tastes that will sequentially be performed on Day 2. In total there will be 5 taste assessments that will be assigned on both days. With the randomization step each volunteer will receive an enrolment number composed of 5 digits. The first two digits reflect the sex and age group and the last three digits incorporate the screening number.

The tablets (L-PZQ and Rac-PZQ ODTs) assessed on Day 1 will be put on the tongue (in the order given from the randomization) each to self-dispersion and at the end of each dispersion the subject will be asked to spit out the content.

Before every taste assessment the volunteer need to fast for about 1 hour. This period can be used to perform the physical examination, eligibility check and randomization.

The following steps will be performed for the first taste assessment:

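### Section 6.3 gives the sequence envelope to both the Investigator and the pharmacist although section 6.10 says the investigator is blinded, and the protocol describes no blinding method for the Day 1 tablets

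*Protocol*

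**What the plan says.** **Who handles the envelope.** Section 6.3 states that "The Investigator or delegate will allocate a randomization number to each subject in each stratification group", and then that, once consent, assent and eligibility are confirmed, "the Investigator will open the next envelope corresponding to the correct gender and age group to assign the sequence". Below Table 2, still in section 6.3, it says: "The pharmacist will perform the randomization by taking the next envelope corresponding to the child's gender and age".

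**What the envelope reveals.** "In the randomization envelope there will be the code for the sequence of taste assessment for all 5 treatments", that is, for both days. Table 2 lists codes F1 and G1 (Day 1) and H2 to N2 (Day 2) with the named formulation in each period. Section 8.2 lists the same codes and orders.

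**Who is blinded.** The title calls the trial single blind, and the synopsis applies that label to each day. Section 6.10 goes further: "All oral suspensions will be drawn into identical syringes which have been wrapped with tape obscuring the content", with the purpose "to minimize bias and blind the subjects and the investigator from the identity of the formulation". Under section 6.11 a study physician who needs the code asks the pharmacist for it.

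**How Day 1 is given.** Section 7.1.2: "The tablets (L-PZQ and Rac-PZQ ODTs) assessed on Day 1 will be put on the tongue". No syringe is involved, and section 6.10 does not mention tablets.

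**The concern.** Two things do not fit together.

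First, the person whom section 6.10 describes as blinded is told in section 6.3 to open the document that breaks the blind. The taped syringes cannot keep the product from someone who already holds the order and a protocol that decodes it.

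Second, the only masking procedure in the protocol belongs to Day 2. The Day 1 contrast between L-PZQ ODT and Rac-PZQ ODT without water is a primary hypothesis (section 8.5.2) with its own power statement (section 8.1), and the protocol does not say how the child or the staff are kept from knowing which tablet is which.

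What is at stake is a subjective score. Children from age 6 mark a 100 mm line under adult supervision (Appendix III). Section 3 records an expectation that the L-PZQ formulation will be the more palatable. Discomfort and other acceptance observations, a secondary endpoint in section 8.3.2, come from the parents or the investigator. Randomised, balanced order protects against period effects. It does not protect against cueing that follows the product, because such cueing adds directly to the treatment contrast.

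**Working it through.** This is mainly a comparison of texts, with one check on the status of Day 1.

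**Step 1: the statements on the envelope and the code.**

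| Place | Statement | Does the investigator know the order? |
|---|---|---|
| 6.3, before Table 2 | Investigator or delegate allocates the randomization number | Possibly; depends on what the number shows |
| 6.3, before Table 2 | Investigator opens the envelope | Yes |
| 6.3, after Table 2 | Pharmacist takes the envelope and randomizes | No |
| 6.7 | Pharmacy prepares all products per period from the randomization list | No |
| 6.10 | Investigator is blinded | No |
| 6.11 | Physician must ask the pharmacist to unblind | No |

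Row 2 cannot stand with rows 3, 5 and 6. Row 1 needs to be aligned with whatever is decided.

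**Step 2: does opening the envelope really unblind?** The code is a letter pair, not a product name. Table 2 and section 8.2 each decode it in full, so envelope plus protocol gives the product in all five periods.

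**Step 3: what section 6.10 covers.** It concerns oral suspensions drawn into syringes, which are treatments C, D and E on Day 2. Treatments A and B on Day 1 are intact ODTs placed on the tongue. Section 6.1 describes both drug substances as white or almost white powders and both products as 150 mg ODTs. It does not say whether the finished tablets look the same. Section 6.6 says that one packaging unit serves several subjects, so no child-specific coded pack is described.

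**Step 4: Day 1 is a powered primary comparison.** Inputs from section 8.1: n = 48, difference 10, within-subject SD 15, two-sided alpha 5%.

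- Standard error = 15 × √(2/48) = 3.06 mm.
- Noncentrality = 10 / 3.06 = 3.27.
- Power from the noncentral t with 46 df = 89.2%, which reproduces the protocol's figure.

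**Step 5: scale of sensitivity, as an illustration only.** The documents give no figure for cueing. If one assumes a product-linked shift of 1, 2 or 3 mm and no true difference, the same calculation puts the chance of a significant Day 1 result at 6.2%, 9.8% or 16.0% instead of 5%. These shifts are assumptions chosen to show the range, not estimates.

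**The case against.** The strongest reply is that the pharmacist route is plainly the intended one. Sections 6.7 and 6.11 and the second half of section 6.3 all point to it, and the sentence on the Investigator looks like a stray. That is a fair reading of the intent, but the protocol is the instruction the site follows, and section 6.3 gives two instructions for one step. It still has to be reconciled.

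A second reply is that single blind permits an unblinded investigator. The label alone would, but section 6.10 names the investigator among those to be blinded.

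A third is that the detail may sit elsewhere. Section 6.2 promises separate preparation and administration instructions for all arms, and sections 6.6 and 6.7 refer to a Packaging Concept and a Pharmacy Manual. None is at hand, and any of them may describe masking for Day 1. This limits the Day 1 point to what the protocol itself describes. It cannot cure the conflict inside section 6.3.

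Stronger readings are tempting and should be resisted:

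- A reader might infer that nobody on the investigating side would be blind. The sentence exposes whoever opens the envelope. Nothing says that the nurse who records discomfort or the adult who supervises the VAS sees it, and on Day 2 the taped syringes still mask the content from the child.
- A reader might infer that the two ODTs can be told apart. The protocol is silent on this.
- A reader might infer that several observer-reported endpoints are affected. Section 8.3 lists one, discomfort and other observations. The taste questionnaire is answered by the child, and adverse event causality is not listed there as an endpoint.
- A reader might take 240 tastings (48 × 5), or 96 on Day 1 (48 × 2), as the size of the problem. These count tastings. They do not measure bias, and the 240 applies only if the Investigator sentence is the one followed.

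**Conclusion.** The point holds in two parts. Section 6.3 contradicts itself, and its Investigator sentence contradicts sections 6.10 and 6.11; followed as written, it defeats the blind that section 6.10 promises for the investigator. This part rests on the text alone and is firm. The second part is that section 6.10 describes no blinding method for Day 1, although Day 1 is labelled single blind and is a powered primary comparison. This is firm as a statement about the protocol, and conditional on the unseen supporting documents as a statement about conduct.

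The direction of any bias is plausible, given the expectation stated in section 3, but its size cannot be derived from the document. The route to the primary endpoint is cueing of the child by informed staff, which is possible but not shown. The matter should be corrected before the first child is randomized. It does not invalidate the design.

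**What to change.** 1. **Section 6.3:** state once that only the pharmacist, who takes no part in tasting or assessment, opens the envelope and holds the sequence code. Remove the sentence that has the Investigator open it, and amend the sentence on the Investigator or delegate allocating a randomization number so that it matches. Check the result against sections 6.10 and 6.11.
2. **Section 6.10:** extend it to Day 1. State whether the two ODTs match in appearance, and have the pharmacist dispense each in a container coded by child and period only. A container hides identity only until the tablet is placed on the tongue, so the statement on appearance is the essential part. If the tablets differ visibly, the protocol should say so and say who remains blinded.
3. **Sections 6.10 or 7.3:** state that those who supervise the VAS and those who record discomfort and adverse events have no access to the code.

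Table 2 need not be moved. Section 8.2 decodes the same codes, and listing sequences in a protocol is ordinary; controlling the envelope does the work.

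The cost is protocol and Pharmacy Manual wording plus simple coded containers. The pharmacist is already in the plan, and neither sample size nor analysis changes.

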**Table 2 Randomization codes and sequences**

| Randomization code | DAY 1                             |                                    |
|--------------------|-----------------------------------|------------------------------------|
|                    |                                   |                                    |
| F1                 | Rac-PZQ ODT put on the tongue (B) | L-PZQ ODT put on the tongue (A)    |
| G1                 | L-PZQ ODT put on the tongue (A)   | Rac--PZQ ODT put on the tongue (B) |
|                    | DAY 2                             |                                    |

|    |                                             |                                             |                                             |
|----|---------------------------------------------|---------------------------------------------|---------------------------------------------|
| H2 | L-PZQ ODT dispersed in water (C)            | Rac-PZQ ODT dispersed in water (D)          | PZQ formulation 150 mg crushed in water (E) |
| J2 | L-PZQ ODT dispersed in water (C)            | PZQ formulation 150 mg crushed in water (E) | Rac-PZQ ODT dispersed in water (D)          |
| K2 | Rac-PZQ ODT dispersed in water (D)          | PZQ formulation 150 mg crushed in water (E) | L-PZQ ODT dispersed in water (C)            |
| L2 | Rac-PZQ ODT dispersed in water (D)          | L-PZQ ODT dispersed in water (C)            | PZQ formulation 150 mg crushed in water (E) |
| M2 | PZQ formulation 150 mg crushed in water (E) | L-PZQ ODT dispersed in water (C)            | Rac-PZQ ODT dispersed in water (D)          |
| N2 | PZQ formulation 150 mg crushed in water (E) | Rac-PZQ ODT dispersed in water (D)          | L-PZQ ODT dispersed in water (C)            |

The pharmacist will perform the randomization by taking the next envelope corresponding to the child's gender and age.

In order to avoid assignment errors the envelopes for boys and girls will be of different colour and the envelopes for the two age groups will also differ (e.g. blue envelopes for boy and age group 6-9 years has a different sticker than age group 9-11). In the randomization envelope there will be the code for the sequence of taste assessment for all 5 treatments (i.e. for both days).

If a volunteer does not show up on Day 2, swallows more than 1 medication or cannot assess all 5 taste assessments he/she will be replaced by a volunteer of the same sex and age group.

## **6.4 Other Drugs to be used in the Trial**

Not applicable.

## **6.5 Concomitant Medications and Therapies**

### **6.5.1 Permitted Medicines**

Any medications (other than those excluded by the clinical trial protocol) that are considered necessary for the subjects' welfare and will not interfere with the trial medication may be given at the Investigator's discretion.

The Investigator will record all concomitant medications taken by the subject during the trial, from the date of signature of informed consent, in the appropriate section of the CRF.

Any additional concomitant therapy that becomes necessary during the trial and any change to concomitant drugs must be recorded in the corresponding section of the CRF, noting the name, dose, duration and indication of each drug.

### **6.5.2 Non-permitted Medicines**

Administration of any investigational product or use of any investigational device 4 weeks prior to first administration of IMP and during the entire clinical trial is not permitted.

Also, any medication from screening until last administration is not allowed without prior approval from the Investigator. No vitamins, supplements or herbal remedies are allowed. Attention should be paid to any drugs or OTC compounds that may affect the taste study assessment.

Any additional concomitant therapy that becomes necessary during the trial must be recorded in the corresponding section of the CRF, noting the name, dose, duration and indication of each drug.

If the administration of a non-permitted concomitant drug becomes necessary during the trial, e.g., because of AEs, the subject should be discontinued from the trial but only after consultation with the Sponsor.

